ask participants in the intervention group how often they accessed the food retailer, about their participation in educational and community building activities, about wasted food and about whether they would have wanted other foods to be provided.

We will perform a cost-effectiveness analysis from a societal perspective that considers direct and indirect costs of the intervention and direct and indirect effects including changes in healthcare utilization. We will assess the economic implications of the potential effects of the intervention including costs associated with primary care, emergency department use, and complications of diabetes based on previous studies of the association between hemoglobin A1c and health outcomes.

We will report demographic characteristics collected at the time of enrollment including age, sex, gender, education level, household income, income source, ethnicity, and medical comorbidities.

We will employ an intention to treat analysis. The primary analysis of the follow-up A1c (follow-up measurement) will be adjusted for baseline hemoglobin A1c and analysed using analysis of covariance (ANCOVA). Binary outcomes will be compared between groups using risk differences with 95% confidence intervals, and chi-squared tests to derive two-sided p-values. Continuous outcomes will be compared between groups using difference in means with 95% confidence intervals, and t-tests to derive two-sided p values. Count outcomes will be analysed using rate ratios from quasi-Poisson models with 95% confidence intervals and two-sided p-values, which will be adjusted for baseline values whenever available. Ordinal outcomes will be analyzed using ordinal regression.

Randomization will be stratified by site. We will report both the unadjusted analysis for the primary outcome and the analysis adjusted for age, sex, whether or not prescribed diabetes oral medicines at baseline, and whether or not prescribed insulin at baseline.

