  - a. (If answered Yes to question 3) How often did this happen? Potential responses are: Almost every month, Some months but not every month, Only 1 or 2 months, Don't know/Refuse to answer
4. In the past 6 months, did you (personally) ever eat less than you felt you should because there wasn't enough money to buy food

5. In the past 6 months, were you (personally) ever hungry but didn't eat because you couldn't afford enough food? Potential responses are: Yes, No, Don't know/Refuse to

Participants can answer affirmatively to 0 to 6 of the questions. We will assess food security status as a binary variable, where less than 2 affirmative responses indicates "food secure" and 2 or more affirmative responses indicates more "food insecure." This is based on Health Canada's approach to interpreting the data from the Household Food Security Survey Module (13). We will also examine food security as a raw score between 0 to 6 (based on the number of affirmatively answered questions) as a sensitivity analysis.

Self-reported financial security is a categorical variable where participants were asked the standard question at follow-up "Do you have trouble making ends meet at the end of the month?" Potential responses were: yes, no and decline to respond.

Self-reported vegetable consumption and self-reported fruit consumption are both categorical variables, measured at both baseline and 6 months. Participants were asked "How often to you eat vegetables?" and "How often do you eat fruits?" Potential responses included: 0 times per day, once per day, twice per day, three times per day, four times per day, five or more times per day, or decline to answer.

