### 6.3 Secondary Outcomes:

1. Serum  $\beta$ -carotene levels (a continuous variable, expressed in units of  $\mu\text{mol/L}$ )
2. Serum ascorbic acid levels (a continuous variable, expressed in units of  $\mu\text{mol/L}$ )
3. Self-reported health status (an ordinal variable with the following categories: very good, good, moderate, bad, and very bad)
4. Self-reported financial security (a binary variable with the following categories: yes and no)
5. Self-reported food security (an ordinal variable with values between 0 to 6 and a binary variable with the following categories: food secure and food insecure)

6. Self-reported vegetable consumption (a count variable with values between 0 to 5 times per day)
7. Self-reported fruit consumption (a count variable with values between 0 to 5 times per day)

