### 8.3 Analysis of secondary outcomes

The continuous outcomes of serum  $\beta$ -carotene and ascorbic acid levels will be compared between groups using difference in means with 95% confidence intervals, and t-tests will be used to derive two-sided  $p$ -values. Alternative non-parametric tests will be used if the data does not meet the assumptions of t-tests and these may include the Wilcoxon Rank Sum test.

The binary outcomes of self-reported financial security and food security status will be compared between groups using risk differences with 95% confidence intervals, and chi-squared tests to derive two-sided  $p$ -values.

The count outcomes of self-reported vegetable and fruit consumption, will be compared between groups using the Wilcoxon rank sum test, where a  $p$ -value of  $<0.05$  will be sufficient to reject the null hypothesis of no difference.

For the ordinal outcomes of self-reported health-status and food-security score ordinal regression will be used using odds ratios with 95% confidence intervals.

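### SAP 8.3 tests vegetable and fruit intake with an unadjusted Wilcoxon test and prespecifies no effect estimate, although baseline intake was collected and the protocol's rule for counts is a baseline-adjusted rate ratio with 95% CI

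*Combined protocol and SAP*

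**What the plan says.** **SAP 8.3 (Analysis of secondary outcomes).** "The count outcomes of self-reported vegetable and fruit consumption, will be compared between groups using the Wilcoxon rank sum test". The only decision rule attached is that a p-value below 0.05 is "sufficient to reject the null hypothesis of no difference". No covariate, estimate or interval is named. The other secondary outcomes in the section each get a mean difference, risk difference or odds ratio with a 95% CI.

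**SAP 6.3 (Secondary Outcomes).** Both items are classed as counts: "Self-reported vegetable consumption (a count variable with values between 0 to 5 times per day") and "Self-reported fruit consumption (a count variable with values between 0 to 5 times per day"). No other outcome in that list is called a count.

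**SAP 5.3 (Data preparation).** The two items are called categorical here, and were "measured at both baseline and 6 months". The top response is five or more times per day.

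**Protocol, analysis paragraphs under Secondary outcome measures.** Counts get "rate ratios from quasi-Poisson models with 95% confidence intervals and two-sided p-values, which will be adjusted for baseline values whenever available". A separate sentence sends ordinal outcomes to ordinal regression and does not mention baseline.

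**SAP 3.2.** Hypotheses 6 and 7 are superiority hypotheses on vegetable and fruit intake.

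**Summary of Changes to the Protocol.** Three amendments are listed, and none concerns this analysis.

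**The concern.** The same question was put to participants at baseline and at 6 months. The baseline answer is normally the best single predictor of the follow-up answer, and using it costs no extra data. A two-sample rank test on the follow-up value leaves it out.

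The second gap is in reporting. A p-value does not say how much intake moved. When p exceeds 0.05, it does not say which increases remain compatible with the data. If an estimate is added later, its scale and model will have been chosen after the plan was fixed. For two of the seven secondary hypotheses the plan therefore gives a test but no prespecified answer to how large the effect is.

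The third gap is consistency. A reader who takes the SAP's count label to the protocol's rule for counts finds a different method, with no reason given for the change.

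**Working it through.** **Step 1. Setting the texts side by side.**

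| Question | Protocol rule for counts | SAP 8.3 for intake |
|---|---|---|
| Method | quasi-Poisson model | Wilcoxon rank sum |
| Baseline value | adjusted for when available | not used |
| Estimate | rate ratio | none named |
| 95% CI | yes | none named |
| p-value | two-sided | p < 0.05 rule |

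The condition that a baseline be available is met (SAP 5.3). If intake is treated as ordinal instead, the protocol's method is ordinal regression. Wilcoxon is not the protocol's method under either classification.

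**Step 2. The only sample size in the documents.** SAP 7 uses a difference of 0.4 and an SD of 1.3 (HbA1c percentage points), alpha 0.05 (two-sided reproduces the figure) and 80% power:

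n per arm = 2 × (1.960 + 0.842)² × (1.3 / 0.4)² = 165.8, so 166 per arm and 332 in total. This matches the SAP.

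With 15% dropout, 332 / 0.85 = 390.6, so 391 against the stated 390, a rounding difference.

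This is the HbA1c requirement. The documents give no such figure for intake, so 166 per arm is borrowed below as a plausible evaluable number.

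**Step 3. Power on a 0–5 scale.** All intake inputs are assumptions: six categories with frequencies 12/33/28/15/7/5%, cut from a latent normal variable; a true shift of 0.3 latent SD; 166 per arm; two-sided 5%. The adjusted analysis is a rank-based ANCOVA on the baseline value, standing in for any baseline-adjusted model.

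| Latent correlation | Wilcoxon | Baseline-adjusted |
|---|---|---|
| 0 | about 74% | no gain |
| 0.2 | about 74% | about 75% |
| 0.3 | about 74% | about 77% |
| 0.4 | about 74% | about 78% |
| 0.5 | about 74% | about 83% |
| 0.6 | about 74% | about 87% |

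Wilcoxon varied between 72% and 75% across settings, so differences of a point or two are simulation noise. Type I error was near 5% for both methods.

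**Step 4. The same check with the protocol's own model.** A second simulation used slightly different frequencies (8/28/32/19/8/5%), a shift of 0.3075 SD and 2,000 trials per setting:

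| Latent correlation | Wilcoxon | Quasi-Poisson, unadjusted | Quasi-Poisson, baseline-adjusted |
|---|---|---|---|
| 0 | 75% | 76% | 76% |
| 0.3 | 76% | 76% | 78% |
| 0.5 | 75% | 77% | 85% |
| 0.6 | 76% | 76% | 89% |
| 0.7 | 75% | 77% | 92% |

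Wilcoxon and the unadjusted quasi-Poisson model are close throughout. Nearly all of the loss therefore comes from leaving out the baseline, not from using ranks.

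**Step 5. Precision on the observed scale.** For a linear adjusted comparison the variance factor is 1 − r², where r is the correlation of the recorded 0–5 values. Cutting the latent variable into the six categories of step 3 weakens the correlation:

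| Latent | Observed r | Variance cut, r² | Equivalent extra participants, 1/(1 − r²) − 1 |
|---|---|---|---|
| 0.4 | 0.367 | about 13% | 1/0.865 − 1 = about 16% |
| 0.5 | 0.461 | about 21% | 1/0.787 − 1 = about 27% |
| 0.6 | 0.556 | about 31% | 1/0.691 − 1 = about 45% |

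**The case against.** **The protocol never calls intake a count.** It lists ordered responses, and its ordinal rule carries no stated baseline adjustment. A reader might infer that the SAP overrode a model the protocol had assigned to these items by name. The documents do not support that, because the link runs through the SAP's own label in 6.3, and 5.3 says categorical. It remains true that the SAP calls the items counts and then does not apply the protocol's rule for counts.

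**Wilcoxon is a sound test here.** It suits a six-level scale with an open top category, and its type I error is near nominal. This stands: the use of ranks is not the fault.

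**The trial could still report the size of any change.** A reader might infer that no effect size will be available. The documents support only that none is prespecified, since nothing bars a description of intake by arm. Beta-carotene and ascorbic acid, which the protocol says correlate with reported intake, already get mean differences with CIs.

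**The loss may be small.** This also stands. At a latent correlation of 0.2 the gain is about one point, and at 0 there is none. A reader might also apply 1 − r² directly to latent correlations of 0.4, 0.5 and 0.6, giving variance cuts of 16%, 25% and 36%, or 19%, 33% and 56% more participants. Those figures overstate the gain on the recorded scale (step 5).

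**The gap is not unique to intake.** SAP 8.3 names no covariate for any secondary outcome, and food security also has a baseline. The missing estimate and CI, however, are peculiar to the two intake items. The vouchers are also no longer restricted to fruit and vegetables, so intake is a less direct target than it was, although both remain listed superiority hypotheses.

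**Conclusion.** The point holds as a modest gap in efficiency and reporting for two of seven secondary outcomes. SAP 8.3 leaves out a baseline measurement that was collected, prespecifies no estimate or interval for hypotheses 6 and 7, and departs without explanation from the protocol's rule for outcomes that the SAP itself calls counts.

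The textual part needs no assumptions. The size of the power loss rests on an assumed shift, category distribution, evaluable number and correlation: from nothing at zero correlation, to about 9 points at a latent correlation of 0.5 (74% against 83%) and about 13 at 0.6 (74% against 87%). The direction holds for any material correlation.

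The validity of the Wilcoxon test and the primary HbA1c analysis are not in question.

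**What to change.** In SAP 8.3, for both intake outcomes:

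1. Restore the protocol's quasi-Poisson model, with arm and the baseline value of the same item as terms. Report the rate ratio, 95% CI and two-sided p-value. A proportional-odds model adjusted for the baseline category, with odds ratio and 95% CI, is an acceptable alternative given the capped top category, and SAP 8.3 already uses ordinal regression elsewhere.
2. Keep the Wilcoxon test as a sensitivity analysis.
3. State how declined or missing baseline intake is handled. The imputation foreseen in SAP 8.2 is for baseline characteristics, and intake is not in the SAP 6.1 list, so this cannot be taken as covered.
4. Use one classification of the items in SAP 5.3 and 6.3.
5. Record the change and its reason, dated before unblinding. SAP 7 reports all 390 participants as recruited, so if unblinding has already happened, label the analysis post hoc.

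The cost is some SAP wording, a little more analysis work and a rule for declined baseline answers. No new data are needed.

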### **Design, Data Collection & Analysis**

The study is an individual participant, 1:1 allocation, two-arm parallel randomized controlled trial. Allocation will be unblinded to participants and clinicians; outcome assessors and adjudicators will be blinded. Randomization will be stratified by condition: “pre-diabetes” (A1c 6.0 to 6.4) versus diabetes (A1c  $\geq$  6.5).

The trial design including the outcomes will be publicly registered and results reported according to CONSORT and TIDier guidance. We will make individual level participant data available when the study is complete (no identifying information about participants).

An established community guidance panel will contribute to developing the plan to implement the intervention and provide direction in study processes, interpretation and recommendations and may also identify potential additions to the study outcomes.

Study personnel will send the clinicians of participants in each group messages, through the electronic health record, at three, four and five months after randomization reminding them that the patient may be due for a hemoglobin A1c measurement. We will also contact participants by phone and email to remind them about having their hemoglobin A1c checked at 5 months.

The intervention period is six months. We will administer a survey after six months which can be completed by phone, by email, in person during a clinic visit or in person at home and will take approximately 15 minutes to complete. A subset of 20 randomly selected intervention group participants will be prompted to report all foods and beverages consumed the prior day using a validated self-administered 24-hour recall as part of this survey. In a separate subset of 20 purposefully selected intervention group participants, we will conduct interviews to capture the experience of the intervention for qualitative analysis. Prior to contacting participants to complete the survey, we will send a reminder notice by email or mail. Participants in both the intervention and control groups will be compensated \$15 for completing the 6 month follow up survey. The subset of 20 participants will be compensated an additional \$20 when they complete the one-on-one interview which will take approximately 20 minutes.

Hemoglobin A1c will be assessed by a review of the electronic primary care record or based on laboratory testing for study purposes if not ordered for clinical purposes.

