###### 2.2 Trial Design

We conducted an open label, parallel two-arm, 1:1 allocation randomized controlled trial. Randomization is stratified by condition: “pre-diabetes” (A1c 6.0 to 6.4) versus diabetes (A1c  $\geq$  6.5).

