### 8.2 Analysis of primary outcome

Hemoglobin A1c will be compared between the intervention and control arm using analysis of covariance (ANCOVA). The covariates will be age, sex, household size, and condition (diabetes versus prediabetes). We will present results of the adjusted and unadjusted models. We will also describe for each group (intervention and control) the baseline, follow-up (6 month) and change (follow-up minus baseline) A1c using mean (with standard deviation) and median (with interquartile range).

In a sub-group analyses, we will assess whether there is a significant interaction between the mean change in hemoglobin A1c and (1) age, (2) sex, (3) condition ("prediabetes" and diabetes), (4) household size, (5) whether prescribed oral diabetes treatment (6) whether prescribed insulin.

We will also use chi-square tests to compare the proportion of participants with "pre-diabetes" (A1c 6.0 to 6.4) at baseline who convert to a normal hemoglobin A1c ( $<6.0$  %) and those who convert to diabetes (A1c  $\geq 6.5$ ), and the number of participants with diabetes at baseline (A1c  $\geq 6.5$ ) who convert to "pre-diabetes" (A1c 6.0 to 6.4) and to normal hemoglobin A1c ( $<6.0$ %).

For the primary analysis, a  $p$ -value of  $<0.05$  will be sufficient to reject the null hypothesis of no difference.

We will address missing outcome data using methods appropriate to their pattern which may include inverse probability weighted analysis. We will address missing baseline characteristic data using methods appropriate to their pattern which may include multiple imputation.

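### SAP 8.3 names no stratification factor or covariate for financial security or self-rated health; the cost is a conservative, probably small loss of power, and the factor itself must first be reconciled

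*Combined protocol and SAP*

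**What the plan says.** Self-rated health and financial security are hypotheses 3 and 4 in SAP 3.2. For financial security, SAP 8.3 states "The binary outcomes of self-reported financial security and food security status will be compared between groups using risk differences with 95% confidence intervals", with "chi-squared tests to derive two-sided" p-values. For self-rated health it states "For the ordinal outcomes of self-reported health-status and food-security score ordinal regression will be used using odds ratios with 95% confidence intervals". The first is a crude comparison. The second gives a model family without its terms.

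Covariates appear only for HbA1c. SAP 8.2 puts condition, household size, age and sex in the primary model. The protocol's list (age, sex, oral diabetes medicines, insulin) also applies only to the primary outcome.

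On the design, SAP 2.2 says "Randomization is stratified by condition", and the protocol under Design, Data Collection & Analysis says "Randomization will be stratified by condition". The analysis paragraphs at the end of the protocol's Secondary outcome measures say "Randomization will be stratified by site".

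SAP 5.3 names baseline survey data for food security and for fruit and vegetable intake. It names none for self-rated health or financial security.

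**The concern.** Stratified randomisation balances a factor between arms. If the factor predicts the outcome, an analysis that leaves it out treats its variation as noise that the design has already removed, and the test then rejects less often than its nominal level. In a logistic or proportional-odds model, omitting a prognostic factor also moves the odds ratio towards 1.

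At stake is some power on two hypotheses that the SAP sets out to test. The sample is fixed at the 390 already recruited, so extra precision can come only from the analysis. For self-rated health there is also a specification gap: if the model's terms are not written down, they could be chosen after results are seen.

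**Working it through.** **Stated figure.** SAP section 7 sizes the trial for HbA1c only: n per arm = 2(1.96 + 0.8416)² × 1.3² / 0.4² = 165.8, so 166 per arm and 332 in total, as stated. 332 / 0.85 = 390.6, against 390 stated. No power or effect size is given for either outcome here. I use 166 evaluable per arm; every other input below is an assumption, because the documents give no values.

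**Financial security.** Assumed: overall risk p = 0.60; prediabetes share w = 0.30 or 0.50; risk gap between conditions g.

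- Variance used by the crude analysis: p(1−p) = 0.24.
- Variance within condition: 0.24 − w(1−w)g².
- SE ratio, crude to stratified: √(0.24 / within variance).
- Difference with 80% nominal power: d = 2.8016 × √(2 × 0.24/166) = 0.151.
- Power with condition: Φ(d/SE_within − 1.96). Without: Φ((d − 1.96 × SE_crude)/SE_within).
- Actual α without: 2[1 − Φ(1.96 × SE_crude/SE_within)].

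Example, w = 0.30 and g = 0.20: within variance = 0.24 − 0.21 × 0.04 = 0.2316; √(0.24/0.2316) = 1.018.

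| Gap (points) | SE too large, w = 0.30; 0.50 | Power without | Power with | Actual α without |
|---|---|---|---|---|
| 10 | 0.44%; 0.52% | 80.1%; 80.1% | 80.3%; 80.4% | 0.0490; 0.0488 |
| 20 | 1.80%; 2.15% | 80.4%; 80.5% | 81.4%; 81.6% | 0.0460; 0.0453 |
| 30 | 4.19%; 5.05% | 81.0%; 81.2% | 83.1%; 83.7% | 0.0411; 0.0395 |

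**Self-rated health, adding condition only.** Simulated proportional-odds models, 1,000 trials per setting, arms balanced within condition. Assumed: 30% prediabetes, categories split 10/30/35/18/7%, voucher odds ratio 1.75.

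| Condition OR | Mean log OR, without → with | Mean reported SE, without → with | Power, without → with |
|---|---|---|---|
| 1.5 | 0.570 → 0.575 | 0.200 → 0.201 | 82.9% → 83.5% |
| 2 | 0.555 → 0.568 | 0.200 → 0.200 | 81.9% → 82.5% |
| 3 | 0.532 → 0.560 | 0.199 → 0.201 | 78.5% → 81.1% |
| 5 | 0.513 → 0.568 | 0.199 → 0.201 | 74.4% → 81.0% |

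Each power figure has a Monte Carlo error of about 1.3 points (√(0.8 × 0.2/1000)); both models were fitted to the same simulated data. The reported SE does not fall on adjustment. The ratio of estimate to SE rises because the log odds ratio rises: at OR 3, 0.532/0.199 = 2.67 against 0.560/0.201 = 2.79. The unadjusted test is conservative because its estimate varied less between simulated trials (SD 0.188 at OR 3) than its reported SE of 0.199. With no voucher effect, rejection without and with condition was 4.7% and 4.9% at OR 2, and 2.9% and 5.1% at OR 5.

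**Self-rated health, adding age, sex and treatment as well.** 2,000 trials per setting. Assumed: 35% prediabetes, voucher odds ratio 1.7, the further covariates combined in one score explaining 5% or 15% of latent variance.

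| Condition OR | Score explains | Power, unadjusted → full model |
|---|---|---|
| 2 | 5% | 73.0% → 75.8% |
| 2 | 15% | 67.2% → 76.4% |
| 3 | 5% | 71.3% → 77.2% |
| 3 | 15% | 65.4% → 75.7% |

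In the last setting with no voucher effect, rejection was 4.6% unadjusted and 5.6% adjusted (Monte Carlo error about 0.5 points).

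**The case against.** The case for leaving SAP 8.3 alone is substantial. These are secondary outcomes with no power target. The crude risk difference is a valid marginal comparison and matches the protocol. Any error is conservative. The ordinal sentence is silent on covariates and does not exclude them. Adjustment changes what the odds ratio estimates, and the marginal odds ratio is a legitimate target. Most of this stands, and it limits the point to a minor one. Silence is not a defence, though: an ordinal model for a stated hypothesis needs its terms written down whichever way the choice goes.

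Three stronger readings are tempting, and the documents do not support them.

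- A reader might infer that the interval for the self-rated health odds ratio would narrow on adjustment. It would not: the reported SE is about 0.199 without condition and 0.201 with it. The overstated-SE argument translates into a narrower interval for the risk difference, not for this odds ratio.
- A reader might infer that material power is certainly lost. That depends on how strongly condition, age, sex and treatment predict these answers, and the documents give no figure. The larger gains come from the assumed further covariates more than from condition.
- A reader might take condition as the settled stratification factor. The protocol also says site. If site was used instead, the sizes above do not measure the cost of ignoring the stratification, and a fix using condition alone would omit the actual factor.

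**Conclusion.** The point holds as a minor matter of efficiency and specification. SAP 8.3 clearly leaves financial security unadjusted and does not state the terms of the self-rated health model, despite stratified randomisation and a primary model that includes condition.

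On the assumptions shown, stratifying financial security by condition gains 0.2 to 0.3 power points at a 10-point gap, about 1 at 20 points and 2 to 2.5 at 30. For self-rated health, condition alone gains 0.6 points at an odds ratio of 1.5 or 2, 2.6 at 3, and 6.6 only at 5. The full covariate set gained about 3 to 10 points where the further covariates explained 5 to 15% of latent variance; if they explain little, the gain falls back to that from condition alone. The unadjusted tests err towards missing an effect, so no false-positive risk arises.

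**What to change.** 1. Reconcile the protocol's design section and SAP 2.2 (condition) with the protocol's analysis paragraphs (site), and state the factor or factors actually used in the randomisation system.
2. Financial security, SAP 8.3: use a Mantel-Haenszel risk difference with 95% CI and a Cochran-Mantel-Haenszel test, stratified by those factor(s).
3. Self-rated health, SAP 8.3: fit the ordinal regression with arm, the stratification factor(s), condition, age, sex, and baseline oral-diabetes-medicine and insulin use. State that the resulting odds ratio is conditional on these terms.
4. Keep the crude results as description, and date the change before outcomes are compared by arm.

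The cost is SAP wording. Condition is known from eligibility; age, sex and insulin are in SAP 6.1; oral diabetes treatment is already a subgroup variable in SAP 8.2. The downsides are that the adjusted odds ratio targets a conditional instead of a marginal effect, and that the gain may be small.
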